**Methods:**

The study is a multicentric randomized controlled trial, which will be conducted across 4 phases in Udupi, Mysuru, and Shivamogga districts of Karnataka. Phase 1 features a cross-sectional study design of 175 farmers to evaluate their baseline knowledge, attitudes, and practices on usage of pesticides. Phase 2 employs semi-structured interviews with 20–30 farmers and 10–20 key stakeholders, including pesticide dealers, scientists from Farm Science Centers [Krishi Vigyan Kendra (KVK)], and joint directors of agriculture to explore pesticide handling approaches, challenges, and community-specific needs while handling pesticides. The findings from Phases 1 and 2 will help in development and validation of an intervention in the form of educational video in Phase 3 which will be piloted. Phase 4 involves implementing the validated intervention and conducting long-term follow-up to assess the impact and sustainability. Phase 4 will be a two-arm, single-blind, parallel-group randomized controlled trial, with villages randomized 1:1 into intervention and control groups. The intervention group will receive a 15–20-minute educational documentary in the local language, while the control group will receive no intervention. The outcomes will be evaluated based on changes in Knowledge, Attitudes, and Practices (KAP) scores, with assessments conducted immediately post intervention, at 6 months, and at 12 months from the date of intervention. These will be correlated with outcomes including quality of life and laboratory parameters.

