## Objectives

The objectives of this study include:

To assess the KAP among farmers and correlate it with respect to health-related Quality of Life (QoL) along with biochemical parameters.To conduct qualitative interview among farmers and respective stakeholders to develop need-based education intervention.To assess the impact of educational intervention on KAP and quality of life through multicentric RCT.

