### Trial design

This study adopts a multi-phase, mixed-methods approach to address pesticide safety practices among farmers in Karnataka state. The study will be conducted in 4 different phases. Phase 1 is an analytical cross-sectional study, designed to evaluate the baseline knowledge, attitudes, and practices (KAP) of farmers using structured questionnaires. Phase 2 involves qualitative face-to-face interviews to gain deeper insights into the behavioural and contextual factors influencing pesticide usage and safety practices.

Phase 3 involves development and validation of need-based education module, where selection of experts will be carried out by purposive sampling technique. Phase 4 is a multicentric RCT, where 3 districts that includes 6 villages will be selected based on randomization. This study will be conducted as a two-arm, single-blind, parallel group with simple randomization of the districts and cluster randomization of farmers. The allocation ratio is 1:1, with one arm receiving the educational intervention and the other serving as a control group with no intervention. The outcomes will be assessed in terms of mean difference with the pre and post assessment in terms of KAP. The trial adopts a superiority framework [33] to assess the effectiveness of the educational intervention in improving pesticide safety knowledge, attitudes, and practices among farmers.

The below Fig. 1 depicts the trial process from recruitment to randomisation.

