### Primary outcomes

The primary outcomes of the trial are (i) Knowledge, Attitude, and Practice (KAP) scores, assessed using a validated KAP questionnaire, and (ii) Quality of Life (QoL) scores, evaluated using the SF-36 Questionnaire. Both outcomes will be measured at baseline, post-intervention, and periodic follow-ups, with results analysed as mean changes over time and correlated with laboratory findings to provide a comprehensive understanding of the intervention’s impact.

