### Participant timeline

The trial will be conducted over a period of 3 years in 4 phases. During the phase 1, with duration of 8 months, 175 farmers will be recruited to assess their baseline knowledge, attitudes, and practices (KAP) regarding pesticide usage, which will be correlated with quality-of-life and biochemical parameters.

In the phase 2, which will last 4 months, around 20 to 30 farmers will participate in qualitative interviews to share their needs and perspectives on pesticide usage patterns, disposal methods, and storage practices. Additionally, 10 to 20 key stakeholders, including pesticide dealers, scientists from Farm Science Centre [Krishi Vigyan Kendra’s (KVK’s)], joint directors of agriculture, assistant director of agriculture, subject matter specialist [SMS] will be involved from the selected villages across different districts, to gather qualitative insights and recommendations regarding pesticide usage patterns.

Following this, phase 3 will be conducted over 6 months, which focuses on the development and validation of the educational module. This phase will be followed by a pilot implementation lasting further 6 months.

The final phase 4 will be executed as a randomized controlled trial (RCT), where the validated educational module will be implemented in the selected villages for a specific duration of 2 months. Participants will be followed up at intervals of 6 months and 12 months. The total duration of phase 4 will be 1 year.

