### Statistical analysis

All data collected through the KAP and QoL questionnaires will be entered into SPSS version 20.0 (IBM, New York, NY, USA) for statistical analysis. Paired t-tests will be performed for continuous variables to compare pre- and post-intervention results. For improvements in quality of life and changes in laboratory parameters, the Wilcoxon Signed Ranks Test will be used. The results from the KAP surveys will be presented as mean ± standard deviation (SD). Qualitative interview data will be analysed using NVivo software, with thematic analysis to identify key patterns, insights and to understand the needs and perception of the farmers. Subgroup analyses based on confounding factors such as age, gender, and education level will be conducted to assess differential effects of the intervention. An intention-to-treat analysis will be performed and per-protocol analysis for participants deviating from the protocol.

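### Correlating KAP and QoL results with laboratory values is given a part in judging the film's impact, but it uses no randomised contrast, and the other analysis stated for QoL and laboratory values is not between-arm either

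*Protocol article*

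**What the plan says.** Two of the listed objectives ask different questions. The first is associational: "To assess the KAP among farmers and correlate it with respect to health-related Quality of Life (QoL) along with biochemical parameters". The third is about effect: "To assess the impact of educational intervention on KAP and quality of life through multicentric RCT". The Participant timeline places the correlation in the Phase 1 survey of 175 farmers, before any film exists; their KAP is measured, "which will be correlated with quality-of-life and biochemical parameters".

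Two other places carry the correlation into the randomised phase. Under Primary outcomes, KAP and SF-36 scores at baseline, after the intervention and at follow-up will have their "results analysed as mean changes over time and correlated with laboratory findings to provide a comprehensive understanding of the intervention’s impact". The abstract's Methods paragraph, directly after the Phase 4 assessment times, says "These will be correlated with outcomes including quality of life and laboratory parameters".

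The Statistical analysis section names paired tests only. For continuous variables: "Paired t-tests will be performed for continuous variables to compare pre- and post-intervention results". For the other measures: "For improvements in quality of life and changes in laboratory parameters, the Wilcoxon Signed Ranks Test will be used". It names no correlation method and no comparison between arms.

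**The concern.** The Primary outcomes wording ties the correlation to the intervention's impact. Impact is a question about film against no film, and randomisation is what allows it to be answered. A correlation between a farmer's scores and the same farmer's blood values does not use the allocation. Its null hypothesis is that the two measures are unrelated across farmers.

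Two errors become possible.

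- Age, gender, education and agricultural experience, which the randomisation section itself calls confounding factors, may influence both KAP and laboratory values. The correlation can then differ from zero although the film did nothing.
- If the film shifts every farmer in its arm by a similar amount, the correlation within that arm does not change, however large the benefit.

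The abstract's Discussion expects better KAP to lead to better quality of life and health. A significant correlation could be cited for that link, although it would be an observational association inside a randomised trial.

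**Working it through.** **Plan's own figure.** There is none for this analysis: no coefficient, target correlation or power is given. The 175 farmers of Phase 1 are not at issue here.

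**Inputs from the protocol article.** 1:1 allocation (Trial design); two-sided 5% level, z = 1.96 (Sample size).

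**Assumptions.** No total is stated for Phase 4, so N = 60, 120 and 174 are used; 174 is close to the Phase 1 number. The background correlation r, the KAP shift a and the laboratory shift d (both in SD units) are assumed. Farmers are treated as independent.

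**Direction 1: the film changes nothing (a = d = 0), but shared causes give correlation r.** By Fisher's transformation, the chance of a significant pooled correlation is about Φ(m − 1.96) + Φ(−m − 1.96), with m = atanh(r) × √(N − 3).

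For r = 0.2, atanh(0.2) = 0.2027:
- N = 60: m = 0.2027 × √57 = 1.53, giving 0.33
- N = 120: m = 0.2027 × √117 = 2.19, giving 0.59
- N = 174: m = 0.2027 × √171 = 2.65, giving 0.755

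| Assumed r | N = 60 | N = 120 | N = 174 |
|---|---|---|---|
| 0.1 | 12% | 19% | 26% |
| 0.2 | 33% | 59% | 75.5% |
| 0.3 | 65% | 92% | 98% |

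Simulation at r = 0.2 agrees: 34%, 58% to 61%, and 75% to 76%. A between-arm t-test on the laboratory value stays at about 5% throughout, as it should.

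**Direction 2: the film helps everyone equally (a = 1, d = 0.5) with no background correlation.** Pooling the arms induces a correlation of

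(a × d / 4) / √[(1 + a²/4)(1 + d²/4)] = 0.125 / √(1.25 × 1.0625) = 0.108.

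The same power formula applies to the pooled test. The between-arm test has approximate power Φ(d × √(N/4) − 1.96), where d × √(N/4) is 1.94, 2.74 and 3.30.

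| Test | N = 60 | N = 120 | N = 174 |
|---|---|---|---|
| Correlation within film arm (simulated) | 5% | 5% | 5% |
| Pooled correlation (formula) | 13% | 22% | 30% |
| Between-arm comparison (formula) | 49% | 78% | 91% |

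Across simulation runs the pooled correlation lies between 12% and 31%, and the between-arm test between 47% and 91%.

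The pooled figure depends on both shifts. At N = 158, equal shifts of 0.5 SD in KAP and laboratory value give 11%, and equal shifts of 0.8 SD give 40%. So the pooled correlation picks up some of the effect, but much less than the direct comparison, which reaches 88% to 90% and about 100% in the same two settings.

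**The other stated analysis.** The Wilcoxon signed-rank test compares each farmer with himself or herself before the film. It addresses change over time, which may come from season, repeated questioning or other causes. It yields no difference between arms for QoL or laboratory values.

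**The case against.** The strongest reply is that the correlation is an adjunct. Primary outcomes puts mean changes first, Trial design says outcomes are assessed by mean differences, and no p-value, coefficient or decision rule is attached to the correlation. That stands. A reader might infer that the trial's claim of effect rests on the correlation, or that the correlation is a planned test of effect. The documents support neither.

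A second reply is that QoL and laboratory changes are also tested directly, by the Wilcoxon test. That is true, so a real benefit would not be hidden by a flat correlation alone. But that test is paired and does not supply the missing arm contrast.

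Third, the Trial design section says "The trial adopts a superiority framework" for knowledge, attitudes and practices. A reader might take superiority to extend to laboratory health measures. It does not: QoL impact comes from the third objective, and laboratory values are in neither outcome list in their own right.

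Fourth, the wording may mean correlating changes rather than levels. Fixed traits confound changes less directly, so r = 0.2 may be too high for that reading. The text does not settle levels or changes, pooled or by arm. An article may leave such details to the full plan, and their absence is not the complaint. Under every reading the null concerns association across farmers.

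Finally, it would be too strong to say that the correlation must be flat when the film works. That holds within an arm under a uniform shift, not in general.

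**Conclusion.** The point holds in limited form. In the randomised phase, a correlation is given a share in explaining impact that it cannot carry, and the only other analysis stated for QoL and laboratory values is a pre-post test. With no film effect the correlation would be significant in about a third to three quarters of trials at r = 0.2, or 12% to 98% over r = 0.1 to 0.3 and the three totals. For a uniform 0.5-SD laboratory gain it has well under half the power of a between-arm comparison.

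These sizes rest on assumed r, effect sizes and Phase 4 numbers. They ignore clustering by village, which would lower the power of the between-arm comparison but would not turn the correlation into a test of effect. The Phase 1 correlation is sound as association and needs no change. Severity is minor to moderate, because the correlation supplements mean changes and does not replace them.

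**What to change.** In the abstract's Methods paragraph and under Primary outcomes, keep the correlation of KAP with QoL and laboratory values as the first objective, in Phase 1, where the Participant timeline already puts it.

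For Phase 4, state that impact on QoL and on laboratory values is read from the difference between randomised arms, adjusted for the baseline value of the same measure and analysed with village as the cluster.

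If a Phase 4 correlation is kept, correlate change with change, adjust for arm, label it exploratory, and say that it is not evidence of the film's effect.

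The cost is rewording in two places and one extra model per outcome. No new data are needed. The downside is that a significant correlation can no longer be cited as impact of the film.

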### Secondary outcomes

The secondary outcomes of this trial include (i) adherence to safe pesticide handling practices, (ii) knowledge on first aid for unintentional or occupational pesticide exposure. Additional outcomes comprise (iii) frequency of direct pesticide exposure, assessed through self-reported practices and associated health hazards during follow-up, and (iv) development and dissemination of a localized educational tool, evaluated qualitatively, to promote sustainable knowledge and practices. These outcomes have been selected for their clinical relevance in addressing the short- and long-term health risks associated with indiscriminate pesticide usage, enhancing overall safety, and fostering effective behavioural change among farmers. These outcomes will be assessed by an investigator through observation of the practices and using the self-reported checklists.

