### Intervention

The primary component of the intervention will be a 15–20-minutes educational documentary in the local language. Topics like safe pesticide usage, proper storage, disposal methods, and associated health risks will be covered in this documentary. These elements will be presented through a story that will be displayed as a short documentary or movie among the farmers. Cluster sampling method will be utilised for selecting participants based on characteristics including age, education, and years of experience with pesticides or agriculture. The intervention will be provided in the intended villages at community centres or village halls.

The control group will not receive any educational intervention during the study period. Participation records will be maintained to track adherence to intervention, and any participant’s decision to withdraw from the study will be documented. If withdrawn, data collected up to the point of withdrawal will be retained for analysis. The appropriate reason will be documented for withdrawal if available.

To maintain the integrity of the study, participants will be requested to refrain from engaging in other pesticide-related educational initiatives, although they may continue their regular farming activities. Adherence to the intervention and pesticide practices will be monitored through regular follow-up calls, personal visits, and collaboration with field officers, community leaders, and local organizations.

The detailed participant timeline has been provided in Fig. 2, following the SPIRIT 2025 format [39] .

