### Blinding

This is a single-blinded, double-arm, parallel-group study design, where only the participants will be blinded to their group assignment (intervention or control). This approach minimizes the risk of performance bias among participants. Outcome assessors, data analysts, and other study personnels will not be blinded as it is an educational interventional study.

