## Methods: data collection, management, and analysis

### Data collection and management

In phase 1, data will be collected in person through face-to-face interactions using baseline questionnaires, including the KAP questionnaire and the SF-36 Quality of Life (QoL) questionnaire from RAND Health. Additionally, qualitative interviews will be conducted, and laboratory tests (blood samples) will be collected from enrolled participants. All quantitative data will be stored in OpenEpi version 3.1 software and later transferred to SPSS version 20.0 (IBM, New York, NY, USA) for statistical analysis.

In phase 2, qualitative interviews will be recorded with prior consent, transcribed, and stored securely on a password-protected device. These recordings will be transcribed and translated to verbatim, and themes and sub-themes will be developed using NVivo software for qualitative analysis.

In phase 3, after developing the educational documentary, its validation will be conducted using a Likert scale (ranging from 1 to 4) and face-to-face focus group discussions (FGDs). These discussions will be recorded, transcribed, translated, and analysed to extract themes and suggestions, which will be incorporated to refine the documentary.

In phase 4, pre- and post-intervention questionnaires will be administered to both the intervention and control groups, mirroring the data collection process from Phase 1. The collected data will be stored in OpenEpi version 3.1 software and subsequently analysed using SPSS version 20.0 (IBM, New York, NY, USA).

Throughout the study, participant identities will remain anonymized, and all data will be coded for confidentiality. At the conclusion of the study, data will be discarded as per study protocols. Missing data, such as those resulting from loss to follow-up or participant withdrawal, will be documented with appropriate justifications and reported in the results.

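### Secondary outcome (iii), exposure frequency, relies on self-report in subjects that the film teaches to one arm only, so the between-arm difference mixes exposure with reporting

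*Protocol article*

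**What the plan says.** All references are to the Protocol article.

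- **Secondary outcomes**, item (iii): "frequency of direct pesticide exposure, assessed through self-reported practices and associated health hazards during follow-up".
- The same section closes with a sentence covering all the secondary outcomes: "These outcomes will be assessed by an investigator through observation of the practices and using the self-reported checklists".
- **Intervention**, on the film's content: "Topics like safe pesticide usage, proper storage, disposal methods, and associated health risks will be covered in this documentary". On the comparator: "The control group will not receive any educational intervention during the study period".
- **Blinding**: "Outcome assessors, data analysts, and other study personnels will not be blinded as it is an educational interventional study". Only participants are described as blinded.
- **Participant timeline**, Phase 4: "Participants will be followed up at intervals of 6 months and 12 months".
- **Primary outcomes**: KAP and SF-36 results are to be "correlated with laboratory findings to provide a comprehensive understanding of the intervention’s impact". **Data collection and management** says, for Phase 1, that "laboratory tests (blood samples) will be collected from enrolled participants". Neither section makes the laboratory results a measure of item (iii).

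**The concern.** Two things are wrong with the outcome as defined.

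**Construct.** The outcome is named as a frequency of exposure, but one of its two stated sources is health complaints. These can follow exposure, but they have other causes too. They do not say how often exposure occurred.

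**Differential measurement.** Both sources, practices and health effects, are subjects of the film, and only the intervention arm sees it. A farmer who has seen it may now recognise a headache or a skin contact as pesticide-related, and so report more. Or the farmer may give the answers the film presented as correct, and so report less unsafe contact. Controls undergo neither shift. Randomisation does not balance a change that treatment itself produces, and a baseline reading does not remove it because the change comes after baseline.

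Among the listed outcomes this is the one named as exposure itself. Readers will be inclined to take a difference as evidence that the film altered contact with pesticides. As defined, the comparison cannot tell that apart from a change in reporting.

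**Working it through.** The article states no rate, effect size or sample size for this outcome, so there is no figure to reproduce. The check has two parts.

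**1. Does another part of the plan supply an independent measure of (iii)?**

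- *Investigator observation* (Secondary outcomes). What is observed is practices. Observation at a visit does not count exposures in the months between visits, and the observers know the allocation (Blinding).
- *Participant blinding* (Blinding). One arm watches a film and the other receives nothing. The film's content reaches the intervention farmers whether or not they are told their arm, so this does not prevent the shift.
- *Laboratory data*. These are tied to KAP and SF-36 under Primary outcomes. They are not assigned to (iii), and the article does not name the analytes.

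So the method stated specifically for (iii) remains self-report.

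**2. How much could a reporting shift matter?** This is an illustration; every input is an assumption. Let p be the true share of farmers exposed and s the share of exposed farmers who report it, with no false reports. Then

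observed ratio = (p_film × s_film) / (p_control × s_control).

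Take p_control = 0.40 and s_control = 0.60, so the observed control share is 0.40 × 0.60 = 0.24.

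*No true effect* (p_film = 0.40, true ratio 1.00):

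- s_film = 0.70: 0.28 / 0.24 = 1.17
- s_film = 0.80: 0.32 / 0.24 = 1.33
- s_film = 0.90: 0.36 / 0.24 = 1.50
- s_film = 0.50: 0.20 / 0.24 = 0.83
- s_film = 0.40: 0.16 / 0.24 = 0.67

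*True benefit* (p_film = 0.30, true ratio 0.75):

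- s_film = 0.70: 0.21 / 0.24 = 0.875, about 0.88
- s_film = 0.80: 0.24 / 0.24 = 1.00
- s_film = 0.90: 0.27 / 0.24 = 1.125, about 1.13
- s_film = 0.50: 0.15 / 0.24 = 0.625
- s_film = 0.40: 0.12 / 0.24 = 0.50

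The benefit vanishes when s_film / s_control reaches 1 / 0.75 = 1.33, and reverses beyond that. For a smaller true benefit (ratio 0.80), reporting of 80% against 60% gives 0.80 × 0.80 / 0.60 = 1.07, and 70% against 60% gives 0.80 × 0.70 / 0.60 = 0.93.

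In this model the observed ratio is the true ratio multiplied by the reporting ratio. The trial data on (iii) give only the product.

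**The case against.** The strongest case against has five parts.

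- *Self-report is not the only source.* The section also provides for investigator observation, and the Intervention section describes monitoring of practices by calls, visits and field officers. This stands in part. Observation is a real second source for practices, but it is unblinded and cannot supply a frequency between visits.
- *The instrument is not shown.* The checklist items may already be concrete, and the article gives no unit for the frequency. The wording could also mean that health effects are recorded alongside exposure, not counted within it. This stands as a limit on what can be claimed. The article is a condensed account, and the absence of the items is not itself a fault. But the sentence as written names health hazards as part of how exposure is assessed.
- *The size is hypothetical.* This stands. A reversal needs a large shift in reporting. With 60% against 70%, a true benefit keeps its direction.
- *Self-report in taught subjects is a general limitation of education trials.* True, but it matters more when the result is named exposure.
- *Concrete items would still be self-reported.* This stands too. They reduce the part of the bias that comes from attributing symptoms, and leave the tendency to give the approved answer.

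A reader might go further and infer that the measure follows what farmers learn and not exposure at all, or that the bias runs in one known direction. The document supports neither. The measure would move with both exposure and reporting. More recognition pushes it up, and learned answers push it down.

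**Conclusion.** The point holds in a limited form. Item (iii) combines self-reported practices with health effects. Both lie in the film's subject matter and only one arm is taught, so a between-arm difference cannot be separated into exposure and reporting. The health-hazard component is also not a frequency of exposure.

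The size is unknown. In the illustration, with control reporting fixed at 60% and film-arm reporting between 40% and 90%, a null effect is observed as anything from 0.67 to 1.50 and a true ratio of 0.75 as anything from 0.50 to 1.13. Those ranges rest wholly on the assumed reporting levels and on there being no false reports.

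The consequence is confined to a secondary outcome. The primary KAP and SF-36 comparisons do not rest on it. The definition should be changed before Phase 4, but the trial does not depend on it.

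**What to change.** Reword item (iii) under Secondary outcomes before Phase 4 begins:

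1. Take health hazards out of the exposure outcome. Report symptoms as a separate descriptive outcome, with a caution that the film can change what farmers attribute to pesticides.
2. Define (iii) as self-reported concrete events within a fixed, recent recall window, with the same wording and the same visits in both arms, expressed per spraying day. Examples are spills onto skin or clothing, and days on which a named protective item was not worn.
3. Label the result self-reported exposure and state that it is not to be read as measured exposure, because socially desirable answering remains.

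The cost is rewording one outcome and a few questionnaire items, with no extra staff or visits. The downsides are a slightly longer questionnaire, symptoms no longer contributing to the exposure outcome, and a more modest conclusion from it.
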